## Methods and analysis

2

This study protocol has been developed in accordance with the Standard Protocol Items: Recommendations for Interventional Trials (SPIRIT) guidelines, adapted for an observational cohort study.

### Study objectives

2.1

#### Primary objective

2.1.1

To determine registry-based incidences of neonatal stroke in the Shenzhen region and to evaluate the long-term neurodevelopmental outcomes of affected children at age 5.

#### Secondary objectives

2.1.2

To characterize the clinical presentation, short-term treatment efficacy, and safety of the three subtypes of neonatal stroke: arterial ischemic stroke, cerebral sinovenous thrombosis, and hemorrhagic stroke.To identify significant prenatal, perinatal, and postnatal risk factors for neonatal stroke, and to develop and validate predictive models for risk stratification using a panel of early biochemical and imaging biomarkers.To analyze regional and institutional variations in the diagnostic, therapeutic, and rehabilitative management of neonatal stroke, and to propose evidence-based strategies for optimizing care and standardizing treatment protocols.

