Prognostication of motor outcome following neonatal stroke has been an active area of research. Magnetic resonance imaging (MRI) assessment of the posterior limb of the internal capsule (PLIC) has been shown to correlate with the development of hemiparesis (11, 12). Quantitative scoring systems such as the Modified Pediatric ASPECTS have also been developed to correlate infarct volume with clinical outcomes (13). Additionally, the Hammersmith Infant Neurological Examination (HINE) and general movements evaluation are validated tools for early prediction of cerebral palsy (12). We acknowledge that this registry enrols only diagnosed cases; therefore, cumulative incidence will be calculated using total live births from all 22 participating hospitals as the denominator. However, this represents a hospital-based cohort rather than true population-based surveillance, and referral patterns may bias incidence estimates.

Shenzhen is particularly suitable as a model region due to its annual birth rate of approximately 200,000 live births, >98% NICU coverage across all districts, universal availability of cranial MRI and video-EEG at all participating hospitals, and the fact that >95% of regional births occur within the 22 study hospitals.

Therefore, establishing a prospective, multicenter cohort and dedicated registry is an urgent and foundational step. Such a resource is essential for accurately defining the disease burden, identifying associations with prenatal and perinatal factors that may inform future interventional studies, and mapping the evolution of neurodevelopmental outcomes from infancy through early childhood. By capturing comprehensive, longitudinal data within a real-world clinical setting, a registry can bridge the critical evidence gap between isolated clinical observations and population-level understanding.

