To address this unmet need, we have designed the Shenzhen Neonatal Stroke Online Registry. In this study, we hypothesize that implementing a standardized, multicenter, prospective cohort will yield accurate epidemiological data, identify key risk factors associated with adverse outcomes, and establish a robust platform for developing prognostic models. We present the protocol for a six-year, prospective, observational cohort study involving 22 hospitals in Shenzhen. The primary objectives are to determine the registry-based incidence of neonatal stroke and to evaluate comprehensive neurodevelopmental outcomes at 5 years of age. Secondary objectives include characterizing stroke subtypes, analyzing current management disparities, and integrating a biobank for future mechanistic research. This protocol aims to provide a replicable model for disease surveillance and to generate high-quality evidence to inform clinical guidelines, optimize care pathways, and ultimately improve long-term outcomes for infants affected by stroke.

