### Study design

2.2

This multicenter, prospective, observational cohort study aims to investigate the long-term neurodevelopmental outcomes of neonates with stroke. The study is planned to run for six years, from January 2025 to December 2030, in Shenzhen, China. The initial network comprises 22 collaborating hospitals, with Shenzhen Children's Hospital as the lead institution and Shenzhen People's Hospital as the primary coordinating center.

The study aims to recruit 300 neonates diagnosed with neonatal stroke, following them prospectively for five years to assess their neurodevelopmental trajectory. Additional hospitals may be included throughout the study period. A detailed study flow diagram is presented in Figure 1.

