#### Secondary outcomes

2.5.2

Survival status at hospital discharge and throughout the 5-year follow-up period.Neurodevelopmental outcomes at 5 years were defined as a composite based on Bayley-4C scores and clinical diagnoses of impairments (e.g., cerebral palsy, epilepsy).Risk factor characterization (prenatal, perinatal, and postnatal).Performance of the developed prognostic prediction model for adverse neurodevelopmental outcomes.

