### Statistical analysis plan

2.7

All analyses will be performed using SPSS (Version 27.0) and R (Version 4.4.1).
Descriptive Statistics: Continuous data will be presented as means ± SD (for normally distributed data) or as medians [IQR] (for non-normally distributed data). Categorical data will be analyzed using Chi-square or Fisher's exact tests.Incidence and Survival Analysis: Registry-based incidence and survival rates will be stratified by gestational age, sex, birth weight, and hospital level.Predictive Model Development:
Predictor Selection: LASSO regression will be used to identify potential predictors.Model Building: Multivariable logistic regression will identify independent factors associated with poor neurodevelopmental outcomes.Model Validation: Internal validation using bootstrap resampling (1,000 repetitions) will assess model performance (discrimination, calibration, and clinical utility).A two-sided *p*-value < 0.05 will be considered statistically significant.

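### Only stroke cases are enrolled, so risk factors for neonatal stroke cannot be identified where no birth denominator exists

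*Protocol article*

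**What the plan says.** Section 2.1.2 of the protocol article sets the objective "To identify significant prenatal, perinatal, and postnatal risk factors for neonatal stroke". The sentence then goes on to predictive models for risk stratification.

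Enrolment is confined to cases. The Introduction states that "this registry enrols only diagnosed cases", and section 2.2 says "The study aims to recruit 300 neonates diagnosed with neonatal stroke". Section 2.3.1 requires stroke confirmed on MRI, and section 2.4.1 takes consent once the diagnosis is definite. Section 2.3.1 also makes a recognised stroke risk factor a condition of entry.

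The only source of information on births without stroke is the incidence denominator. According to the Introduction, "cumulative incidence will be calculated using total live births from all 22 participating hospitals as the denominator". Section 2.7 adds: "Registry-based incidence and survival rates will be stratified by gestational age, sex, birth weight, and hospital level".

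The one multivariable analysis in section 2.7 is a logistic model for poor neurodevelopmental outcome. This matches the hypothesis in the Introduction, which is to "identify key risk factors associated with adverse outcomes". Section 2.5.2 lists risk factors only as something to be characterized.

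**The concern.** A risk factor for stroke is one that is more common in infants who have a stroke than in those who do not. A cohort made up entirely of cases supplies one side of that comparison. What it can supply is the frequency of each factor among cases and the association of each factor with outcome after stroke. The second is a prognostic question. A factor may predict outcome without affecting the risk of stroke, and the reverse is equally possible.

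The protocol words the question in three ways: aetiological in section 2.1.2, prognostic in the Introduction, and descriptive in section 2.5.2. Only the last two match the data for most of the factors collected. If the aetiological wording stays, a report written to the objective would have to present case frequencies or prognostic associations as an answer to a question that they do not address. The Discussion hopes that the study will inform the care of pregnant women with risk factors and the planning of delivery, so readers are likely to take the word risk literally.

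**Working it through.** **1. What the study is sized for.** Section 2.6 gives 300 enrolled, 10% mortality, 20% loss to follow-up and a 30% adverse outcome rate.

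- Evaluable: 300 × (1 − 0.10 − 0.20) = 210, as stated.
- Events: 210 × 0.30 = 63, within the stated 60 to 80.

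These figures reproduce. All of them count adverse outcomes among cases. The planned number of stroke-free comparators is 0, and no figure in the document supports a comparison of stroke with no stroke.

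**2. Whether case data can identify the effect.** Let a be the proportion of cases with a factor and p the proportion of births with it. The risk ratio for stroke is

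RR = (a / p) / ((1 − a) / (1 − p)).

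If p is taken in stroke-free births, the same expression is the odds ratio. For an outcome this rare the two practically coincide. The registry observes a and not p. The document gives neither value for any factor, so as an assumption take a = 0.20 and vary p:

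| p (assumed) | Calculation | RR |
|---|---|---|
| 0.05 | (0.20/0.05) / (0.80/0.95) | 4.75 |
| 0.10 | (0.20/0.10) / (0.80/0.90) | 2.25 |
| 0.20 | (0.20/0.20) / (0.80/0.80) | 1.00 |
| 0.30 | (0.20/0.30) / (0.80/0.70) | 0.58 |

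The registry data are the same in every row. Neither the size nor the direction of the effect is determined, and more cases would only estimate a more precisely.

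**3. Where p might be known.** Section 2.7 stratifies incidence by gestational age, sex, birth weight and hospital level. If the 22 hospitals supply live births by stratum, a crude rate ratio is available for each of these four. The Introduction promises total live births only, so the stratum counts are implied by section 2.7 but not described. Counts for one variable at a time support crude ratios. A multivariable rate model would need births cross-classified by the covariates, which the document does not show.

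**4. Limits on those crude ratios.**

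- Section 2.3.1 excludes infants below 28 weeks, but the denominator is all live births. Births below 28 weeks would add to the denominator and could not add a case.
- Section 2.4.4 defines hemorrhagic stroke in term infants only, while section 2.3.1 admits infants from 28 weeks. Read literally, the preterm strata contain no hemorrhagic cases by definition. An all-stroke rate ratio for gestational age is then pushed towards lower risk in preterm infants, and birth weight follows through its link with gestational age.

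**5. What the entry criterion does to frequencies.** If a share s of all strokes has at least one recognised risk factor, and a given recognised factor occurs in a proportion f of all strokes, its frequency among enrolled cases is f / s, which is at least f. Case frequencies are therefore conditional on the entry rule and cannot be read as frequencies in neonatal stroke generally.

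**The case against.** The strongest objection is that stroke risk is not wholly out of reach. A reader might infer from the case-only enrolment that the registry can say nothing beyond prognosis. The documents do not support that: the stratified incidence in section 2.7 permits crude comparisons for four variables if the birth counts exist. This part of the objection stands and limits the point to factors without a birth denominator.

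A reader might also infer that the sponsor intends to present prognostic associations as causes of stroke. No section says so. Section 2.5.2 speaks of characterization, the Introduction of associations that may inform later interventional studies, and the Discussion concedes that the design is limited in establishing causality. The remark on pregnant women and delivery planning is a general expected benefit and is not tied to the regression model. These caveats soften the predicted harm. They do not supply the missing comparison, because an unadjusted, non-causal association with stroke needs exposure data on stroke-free births too.

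Two other defences do not succeed. A separate analysis plan could not repair the gap from the enrolled cases, since the protocol itself fixes who is enrolled. The MRI screening of at-risk neonates in section 2.3.1 is not a control group either: only asymptomatic infarctions are to be documented, no data on screen-negative infants are described, and every screened infant has a risk factor.

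**Conclusion.** The point holds in limited form. For factors without a birth denominator, such as maternal disease, congenital heart disease, sepsis and polycythemia, the objective as worded in section 2.1.2 cannot be met at any sample size. For gestational age, sex, birth weight and hospital level, crude comparisons are possible if live births are available by stratum. They are subject to the limits shown above and to the protocol's own caveat that referral may bias incidence.

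The conclusion rests on the protocol's statement that it enrols cases only and on the absence of any described exposure data for stroke-free births. It does not rest on the 20% and 5% to 30% prevalences. Those are assumptions that show the principle and do not measure an error in this study.

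The point affects one secondary objective. The primary outcome, the sample size and the prognostic model do not depend on it.

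**What to change.** - **Reword the objective in section 2.1.2.** For example: to describe how often prenatal, perinatal and postnatal factors occur among enrolled cases, and to identify factors prognostic for adverse outcome. Bring the Introduction and section 2.5.2 into line.
- **State the condition on frequencies.** Say that factor frequencies are conditional on the entry requirement for a recognised risk factor, unless that criterion in section 2.3.1 is reconciled with the descriptive aim.
- **Limit claims about risk of stroke.** Report crude incidence rate ratios only for variables with stratum-specific live-birth counts, with the denominator restricted to births of at least 28 weeks.
- **Report gestational age and birth weight by stroke subtype.** First reconcile the term-only hemorrhagic definition in section 2.4.4 with the 28-week limit in section 2.3.1. The Discussion already plans subtype-specific analyses for all primary and secondary outcomes.
- **Add other factors conditionally.** Include gestational diabetes, hypertension or others only where the hospitals supply aggregate delivery counts for them.

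The cost is a narrower claim and a request to the 22 hospitals for stratified birth counts. Case recruitment and follow-up need not change for the rewording, though reconciling the entry criterion may alter who is eligible.

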### Study design

2.2

This multicenter, prospective, observational cohort study aims to investigate the long-term neurodevelopmental outcomes of neonates with stroke. The study is planned to run for six years, from January 2025 to December 2030, in Shenzhen, China. The initial network comprises 22 collaborating hospitals, with Shenzhen Children's Hospital as the lead institution and Shenzhen People's Hospital as the primary coordinating center.

The study aims to recruit 300 neonates diagnosed with neonatal stroke, following them prospectively for five years to assess their neurodevelopmental trajectory. Additional hospitals may be included throughout the study period. A detailed study flow diagram is presented in Figure 1.

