**Methods and analysis:**

This multicenter, prospective, observational cohort study aims to enroll 300 neonates diagnosed with stroke, including arterial ischemic, hemorrhagic, and cerebral venous sinus thrombosis subtypes from a network of 22 hospitals in Shenzhen, China, between January 2025 and December 2030. Data collection will utilize standardized electronic case report forms (eCRFs), initially managed via a uniform digital system (
Supplementary File 1), with a planned transition to a secure web-based registry for broader access. Participants will undergo longitudinal follow-up until age five, with neurodevelopmental outcomes assessed using the Bayley Scales of Infant and Toddler Development (4th Ed., Chinese Version), 3T cranial MRI, and video-EEG. To explore the metabolic-inflammatory nexus of neonatal injury, placental pathology will be integrated into the clinical data, and a biobank of stool and breast milk samples will be established. The primary outcome is the registry-based incidence of neonatal stroke. In contrast, secondary outcomes include characterizing clinical subtypes, identifying prenatal/perinatal risk factors, and developing and internally validating a robust prognostic prediction model.

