A central barrier to improving care is the profound lack of prospective, high-quality data on disease epidemiology and natural history (8). While countries such as the United Kingdom, Canada, and Australia have established national neonatal stroke registries to provide continuous, standardized monitoring of aetiology and outcomes (9, 10), such systematic data-collection initiatives are absent in China. Several other countries have successfully developed neonatal and infantile thrombosis registries; for example, the Italian Registry of Infantile Thrombosis (RITI) has provided valuable lessons regarding multicenter collaboration, data standardization, and the challenges of prospective data collection (9). Fragmented, retrospective studies and significant discrepancies in reported incidence rates characterize the existing evidence. For instance, a multicenter study in Beijing reported a rate of 1 in 2,660 (10), whereas a retrospective review across Shenzhen reported a much lower rate of 1 in 8,373 (10). These discrepancies likely reflect differences in case ascertainment (active surveillance vs. retrospective chart review), imaging protocols (universal MRI vs. selective cranial ultrasound), and referral patterns to tertiary centres, rather than true geographic variation in disease frequency. Furthermore, the long-term neurodevelopmental trajectory for survivors, a critical endpoint for families and healthcare systems, is poorly documented, and clinical management, especially for hemorrhagic and venous stroke subtypes, lacks consensus guidelines, leading to potentially inconsistent care.

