### Sample size calculation

2.6

Assuming a 30% neurodevelopmental outcome rate at 5 years (based on published literature), a final sample of approximately 210 evaluable participants would yield 60–80 outcome events. With a maximum of 6–8 candidate predictors, this yields an events-per-variable ratio of approximately 10, exceeding the recommended minimum for logistic regression to avoid overfitting. Internal validation will be performed using bootstrap resampling (1,000 repetitions) to estimate optimism-corrected performance. Total enrollment of 300 accounts, with 10% mortality and 20% loss to follow-up, and the understanding that the final evaluable sample will be approximately 210 participants.

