Additionally, this study underscores the importance of multidisciplinary collaboration and the critical role of follow-up care in early rehabilitation. By emphasizing early diagnosis, intervention, and long-term follow-up, this research will contribute to a more refined and integrated management system for both perinatal medicine and pediatric care. The anticipated outcomes of this study not only hold promise for reducing the financial and emotional burdens faced by families but also offer significant improvements to national health standards, particularly by enhancing the quality of care for neonatal stroke across China.

However, it is important to acknowledge several limitations of this study. As an observational design, it cannot control for all potential confounding variables, limiting its ability to establish causality. The five-year follow-up period is prone to attrition bias, especially if dropouts are associated with disease severity or socioeconomic factors. Despite standardized protocols, the manual data entry across multiple institutions is vulnerable to inconsistencies and inter-rater variability. Furthermore, the findings may have limited generalizability outside of Shenzhen due to regional differences in demographics, healthcare access, and clinical practices. Moreover, during the 5-year enrollment and follow-up period, MRI protocols, neonatal care standards, and antiepileptic treatment strategies may evolve, potentially influencing outcomes. We will document any major practice changes and adjust analyses accordingly. These limitations should be considered when interpreting the study results and formulating future research directions.

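### Enrolment and the whole study share one end date, December 2030, so the 210 evaluable children and 60–80 events in section 2.6 hold only if follow-up continues to about December 2035

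*Protocol article*

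**What the plan says.** The protocol article dates the study in four places.

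- **Abstract, Methods and analysis:** 300 neonates are to be enrolled "from a network of 22 hospitals in Shenzhen, China, between January 2025 and December 2030", with follow-up to age five. No date is given for the end of follow-up.
- **Introduction, last paragraph:** "We present the protocol for a six-year, prospective, observational cohort study involving 22 hospitals in Shenzhen".
- **Section 2.2, Study design:** "The study is planned to run for six years, from January 2025 to December 2030, in Shenzhen, China". The same section plans to recruit 300 neonates, "following them prospectively for five years to assess their neurodevelopmental trajectory".
- **Discussion, limitations:** practice may change "during the 5-year enrollment and follow-up period".

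Section 2.4.6 and Table 1 place the last visit at 5 years corrected age. Section 2.6 assumes a 30% outcome rate at 5 years, takes off 10% for death and 20% for loss, and concludes that "the final evaluable sample will be approximately 210 participants". It expects 60–80 events and allows 6–8 candidate predictors, at about 10 events per variable.

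**The concern.** Six years of enrolment followed by five years of follow-up for the last child takes about eleven years, but the article calls the whole study six years long. Section 2.6 deducts for death and for loss but nothing for children who are too young when the study ends. Its 210 therefore assumes that all 300 have time to reach the 5-year visit.

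Three items rest on that visit: the second part of the primary objective (section 2.1.1), the 5-year neurodevelopmental secondary outcome, and the prognostic model (both section 2.5.2). If data collection stops on the stated date, these would use a small, early-born part of the cohort, and the events-per-variable argument in section 2.6 would no longer apply.

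**Working it through.** **Inputs from the article.** Enrolment of 300 from January 2025 to December 2030 (abstract); study ends December 2030 (2.2); last visit at 5 years corrected age (2.4.6); losses of 10% and 20%, 30% outcome rate, 6–8 predictors (2.6); "annual birth rate of approximately 200,000 live births", with more than 95% of births in the 22 hospitals (Introduction). Incidence figures, also in the Introduction: 1 in 3,000 to 1 in 5,000 for neonatal stroke, 1 in 2,660 in Beijing, 1 in 8,373 in Shenzhen, and 1 in 1,100 as the highest perinatal rate.

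**Step 1: reproduce the plan's figures.**
- Evaluable: 300 × (1 − 0.10 − 0.20) = 210. Applying the losses in sequence gives 300 × 0.90 × 0.80 = 216.
- Events: 210 × 0.30 = 63, near the lower end of 60–80.

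The arithmetic reproduces, provided that every enrolled child can reach the 5-year visit.

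**Step 2: calendar cut-off.** To be 5 by December 2030 a child must be born by December 2025. The cut-off is date of birth, not of enrolment: an infant born in late December 2025 and enrolled within 28 days, in January 2026, still qualifies if born at term. For preterm infants it falls slightly earlier, because ages are corrected.

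**Step 3: uniform accrual (assumption).**
- Children able to reach 5 years: 300 × 1/6 = 50.
- Evaluable: 50 × 0.70 = 35 (36 with sequential losses).
- Events: 35 × 0.30 = 10.5 (10.8 with 36).
- Events per variable: 10.5 / 8 = 1.3 to 10.8 / 6 = 1.8.

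**Step 4: the article's own births and rates, without assuming uniform accrual to 300.** Births in the network: 200,000 × 0.95 = 190,000 a year. Cases in 2025 = 190,000 × rate; evaluable = cases × 0.70; events = evaluable × 0.30. Every case is counted as enrolled, which is generous.

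| Rate | Cases in 2025 | Evaluable at 5 years | Events |
|---|---|---|---|
| 1 in 8,373 (Shenzhen) | 23 | 16 | 5 |
| 1 in 5,000 (neonatal, low) | 38 | 27 | 8 |
| 1 in 3,000 (neonatal, high) | 63 | 44 | 13 |
| 1 in 2,660 (Beijing) | 71 | 50 | 15 |
| 1 in 1,100 (perinatal, highest) | 173 | 121 | 36 |

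**Step 5: can early recruitment rescue the 210?** All 300 would have to be born in 2025. That needs 190,000 / 300, or 1 in 633 (1 in 667 if the hospitals cover every birth: 200,000 / 300). Every rate in the article is lower.

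**Step 6: the other reading.** If December 2030 closes enrolment only, the last child reaches 5 years in about December 2035. The 210 and 63 then stand, provided that 300 are enrolled.

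**The case against.** The strongest reply is that December 2030 was meant to close recruitment only. The abstract ties the dates to enrolment and mentions follow-up to age five separately, and section 2.2 promises five years for each recruit. On that reading the sample size is sound. This stands as a plausible account of intent, so a reader should not infer that the 210 are unattainable outright. It does not remove the conflict: the Introduction and section 2.2 both give six years as the length of the whole study, and no later date appears. The flow diagram and schematic are not shown and may carry a timeline, but the text would still contradict itself.

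Other limits also stand.

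- Incidence is the only primary outcome in section 2.5.1, and 5-year neurodevelopment is listed as secondary in 2.5.2. It would be wrong to infer that the primary outcome is undermined.
- A model on about 10 events would be unreliable. It would not be impossible to fit.
- The Discussion phrase is loose wording in a remark on practice change, and the same paragraph also speaks of a five-year follow-up. It needs tidying but is weak evidence of a third timeline.
- A reader might go on to argue that 300 cases cannot be found in six years. The article does not support that: 6 × 190,000 / 300 gives 1 in 3,800, inside its neonatal range. The Introduction attributes the low Shenzhen rate to a difference in case ascertainment. Case yield is a separate and weaker question.

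**Conclusion.** The point holds in conditional form. As written, enrolment and study end on the same date, which is incompatible with a 5-year visit for all 300. If follow-up stops in December 2030, the evaluable number falls from 210 to about 35 under uniform accrual, or 16–50 across the neonatal, Beijing and Shenzhen rates, with 5–15 events. Even the highest perinatal rate gives only about 121 evaluable and 36 events. These figures carry over the plan's 30% losses and 30% outcome rate. Uniform accrual is my assumption, but the shortfall does not depend on it, because no cited rate would bring 300 births with stroke into 2025. If follow-up runs to about December 2035, the 210 is attainable once 300 are enrolled, and what remains is a correction of the dates. Either way the article needs changing, because a reader cannot tell which timeline section 2.6 relies on.

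**What to change.** State the end of enrolment and the end of follow-up as two separate dates, consistently in the abstract, the Introduction, section 2.2 and the Discussion. For example: enrolment to December 2030, and the last 5-year corrected-age visit in about December 2035, slightly later for preterm infants. Say that the 5-year and prediction-model analyses run only after that visit.

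If December 2030 is a hard close, recompute in section 2.6 the evaluable number, the expected events and the number of predictors for the children who can reach the analysed age by then. Should an earlier age be analysed, its loss and event rates need their own justification, since the plan's 30% figures are given for 5 years.

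The cost is either a later final analysis with up to five more years of visits and oversight, or less favourable stated figures. The incidence analysis need not change.
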